### Randomization and allocation concealment

Enrolled peanut- or tree nut-allergic patients will be randomized in a 1:1 ratio into one of two dietary intervention groups (liberated diet or complete allergen avoidance). Randomization will be stratified for age (1–5, 6–17, 18–67 years of age), allergen (peanut, tree nut), and threshold level at initial OFC (5th–6th, 7th–repetitive cumulative dose). The randomization list is computer-generated (SAS version 9.4, SAS Institute Inc., Cary, NC, USA) by the trial statistician and implemented within the REDCap database system by the data manager. Allocation of patients will be done by authorized study personnel using REDCap (Research Electronic Data Capture). Allocation concealment is assured as the result of the randomization will only be revealed after a patient is enrolled into the trial.

### Study procedures

Children and adults with a suspected or known primary peanut and/or tree nut allergy planning to undergo an oral peanut and/or tree nut (re-)challenge will be informed about the study. Before any study-specific procedure, written informed consent will be obtained from the subject or the subject’s parents/legal guardian according to participant’s age.

During the screening visit, the in- and exclusion criteria will be checked. Information on demographics, subject/household characteristics, relevant medical and allergy history, concomitant medication, dietary (food allergen exposure) history will be recorded. In addition, anthropometric measurements and a physical examination will be performed. In the case of eczema, severity will be assessed by SCORAD [33] and EASI score [34]. The investigators who assess the eczema status will be trained before delegation to the study team. A skin prick test will be performed with peanut (using roasted peanut and peanut extract), hazelnut (using raw and roasted hazelnut), cashew nut (using raw cashew nut), and walnut (using raw walnut) as well as a positive (1% histamine) and negative (0,9% NaCl) control (all extracts: ALK-Abelló, Germany). In addition, in case of suspected or diagnosed allergic rhinoconjunctivitis and/or allergic asthma, a skin prick test will be performed with aeroallergens (birch, mugwort, timothy, house dust mite, cat epithelium) at screening to assess baseline sensitization to aeroallergens. Study staff performing skin prick test will be trained before delegation to the study team. Blood, skin swabs (using DNA/ RNA Shield; Zymo Research, Irvine, CA, USA), stool (using OMNIgene-GUT tubes, OMR-200; DNA Genotek, Ontario, Canada), bed and living room house dust (using dustream® collector DU-ST-1; Indoor Biotechnologies LTD, Cardiff, UK), and saliva (using SalivaBio Swab; Suffolk, Great Britain) samples will be collected for mechanistic subprojects. Standard operating procedures are in place for biosample collection and study staff will be trained before delegation to the study team. Patients will be instructed how to collect stool and dust samples and written instructions will be given. Transepidermal water loss (TEWL) will be measured three times in a row (Tewameter TM 300 or Tewameter TM Hex, Courage + Khazaka electronic GmbH, Germany). Study staff assessing TEWL will be trained before delegated to the study. Eligible participants will undergo their planned OFC with peanut and/or tree nuts for clinical purpose. Vital sign measurement (temperature, pulse, blood pressure, oxygen saturation) will be performed prior to each food challenge. The food challenge, preferably double-blinded, placebo-controlled, are performed in accordance with clinical routine practice of the Charité-Universitätsmedizin Berlin, based on PRACTALL international guidelines for OFCs and stopped using standardized stopping criteria based on PRACTALL guidelines [32]. Roasted, defatted peanut flour, defatted hazelnut flour, crushed cashew, or walnuts (from store-bought whole nuts) will be used for OFC. In case of absence of any objective, allergic symptoms up to seven increasing dose steps at 30-min intervals using a semi log scale ranging approximately from 3 mg to 3 g food protein (depending on the individual allergen) followed by a cumulative dose up to 4.5 g food protein on another day will be administered. Dose steps and the corresponding allergen amounts used for OFCs with peanut or individual tree nuts are displayed in Appendix of the full protocol. Severity of objective immediate-type allergic reactions will be scored according to the grading system for food-induced anaphylaxis published by Sampson [35]. Depending on the outcome of the food challenge, subjects will be included in the TINA study as follows:
Subjects with a positive oral peanut and/or tree nut challenge but who are able to tolerate at least the 5th challenge dose of peanut and/or tree nut will be enrolled into the TINA RCT (part I).Subjects with a negative oral peanut and/or tree nut challenge (successfully consuming and tolerating the repetitive cumulative dose of peanut and/or tree nut) will be enrolled into the TINA cohort study (part II).Subjects with a positive oral peanut and/or tree nut challenge reacting below the 5th dose will be considered as screening failures and will not be enrolled in the study.

#### Randomized controlled trial

At visit 1 (V1) patients with peanut and/or tree nut allergy eligible for the RCT will be randomized into two groups (Fig. 1) “liberated diet group” or “complete allergen avoidance group.” Patients following the liberated diet will get their first peanut or tree nut meal under medical supervision at the study center. They will be instructed to contact the study site by phone in the case of any objective immediate-type allergic reactions to food (either to the dietary regime or due to exposure to (other) food allergens) or recurrent GI symptoms. Patients will be asked to maintain a diary from V1 onwards and are called 2 weeks after V1 (PC1) to investigate compliance and tolerability of the dietary regime and to promote retention. Patients are required to visit the study site after 4 months (V2), 8 months (V3) and 12 months (V4) (Fig. 1, Table 1). At V2, V3, and V4, change of medical and allergy history, concomitant medication, family, and household characteristics will be recorded. In addition, anthropometric measurements and a physical examination will be performed including, in the case of eczema, its severity by SCORAD and EASI score. At V2 and V3 blood (adults only), stool, dust, and saliva samples will be collected and TEWL will be measured. Furthermore, patients randomized in the “liberated diet group” will be allowed to increase the small peanut or tree nut meal if the amounts consumed thus far were well tolerated. The first consumption of the next higher amount will be performed at the study center under medical supervision. Two weeks after V2 and V3, patients will be called (PC2 and PC3) to investigate compliance and tolerability and to promote retention. At V4, another skin prick test and oral challenge to peanut and/or tree nut will be performed (as described above), and blood, skin swab, stool, dust, and saliva samples will be collected.

**Table 1 Tab1:**
[figure not shown]
SPIRIT (Standard Protocol Items: Recommendations for Interventional Trials) figure showing important events and their respective time points during the study period in the randomized controlled trial (RCT)

Abbreviations: *V* Visit, *PC* Phone call, *SCORAD* Scoring atopic dermatitis, *EASI* Eczema area and severity index, *TEWL* Transepidermal water loss measurement, *SPT* Skin prick testing, *GI* Gastrointestinal, *I-C* Intervention-consumption group

* = Screening period can last up to 14 days and V1 might be on the last day of the screening period. The first day of the oral food challenge is defined as the first day of the screening period

1 = bed only

2 = adults only

3 = anytime between PC3 and V4

Generic and disease-specific quality of life questionnaires (PedsQL, EQ-5D, FAQLQ, and FAIM according to age) will be conducted before and 2 weeks after V1, anytime between PC3 and V4, as well as 4 weeks after V4 (remainder at PC4). The FAQLQ is a self-reported, food allergy-specific instrument intended to assess patients’ health-related quality of life and validated for different age groups [36–39]. FAIM is a food allergy independent measure reflecting the patient’s perceived food allergy severity and food allergy-related risk [40]. The validated generic quality of life questionnaires PedsQL and EQ-5D (assessed according to age) are assessed to compare the influence of food allergy with other various diseases on health-related quality of life [41, 42]. Eating habits will be assessed by questionnaire at screening, V2, anytime between PC3 and V4, as well as 4 weeks after V4. Burden of dietary behavior will be assessed using a visual analog scale at two time points during the intervention (V2 and between PC3 and V4). To assess possible GI complaints at screening, V2, V3, and V4, as well as in case of reported recurrent GI symptoms, the PEESS (Pediatric Eosinophilic Esophagitis Symptom Score) questionnaire will be filled out [43].

In case of discontinuation or deviation from the intervention protocol, all participants are encouraged to maintain the scheduled visits or phone calls and collection of all possible data is planned.

#### Cohort study

At V1, eligible subjects with challenge-proven tolerance to peanut and/or tree nut will be included in the cohort study (Fig. 1). Participants will be instructed to contact the study site by phone in the case of any objective immediate-type allergic reactions to food or recurrent GI symptoms. Participants will be contacted by phone 2 weeks, 4 months, and 8 months after V1 (PC1, PC2, PC3) to investigate compliance and tolerability concerning introduction and regular consumption of peanut and/or tree nut using a standardized questionnaire (Fig. 1, Table 2). Participants are required to visit the study site after 12 months (V4). At V4, change in medical and allergy history, concomitant medication, family and household characteristics will be recorded, compliance and tolerability will be assessed using a standardized questionnaire, anthropometric measurements and a physical examination will be performed including, in the case of eczema, its severity by SCORAD and EASI score. In addition, blood, skin swabs, stool, dust, and saliva samples will be collected and TEWL will be measured. Furthermore, participants will be fed one serving of peanut and/or tree nut (corresponding to the repetitive cumulative peanut and/or tree nut dose tolerated at entry food challenge) under medical supervision.

**Table 2 Tab2:** Adapted SPIRIT (Standard Protocol Items: Recommendations for Interventional Trials) figure showing important events and their respective time points during the study period in the cohort study

	Study period					
	Enrolment	Observation				
Visit/Phone Call	Screening including V1^**a**^	PC 1	PC2	PC3	V4	PC4
Time point (months)	0	0.5	4	8	12	13
ENROLMENT:						
Informed consent	x					
Eligibility screen	x					
ASSESMENTS:						
Demographics/subject characteristics	x					
Household/family characteristics	x				x	
Medical and allergy history	x				x	
Dietary history	x					
Physical Examination	x				x	
SCORAD, EASI score	x				x	
TEWL	x				x	
SPT	x				x	
Skin swab	x				x	
Saliva sampling	x				x	
Stool sampling	x				x	
Dust sampling	x				x	
Blood sampling	x				x	
Quality of life questionnaires	x	x		x^b^		x
Questionnaire for GI complaints	x		x	x	x	
Eating habits questionnaire	x			x^b^		
Dietary compliance questionnaire			x	x	x	
Burden of dietary behavior questionnaire		x		x^b^		
Oral food challenge	x				x^c^	
Review of concomitant medication		x	x	x	x	
Review of compliance and tolerance		x	x	x	x	

Abbreviations: *V* Visit, *PC* Phone call, *SCORAD* Scoring atopic dermatitis, *EASI* Eczema area and severity index, *TEWL* Transepidermal water loss measurement, *SPT* Skin prick testing, *GI* Gastointestinal

^a^ = Screening period including V1 can last up to 14 days. The first day of the oral food challenge is defined as the first day of the screening period

^b^ = anytime between PC3 and V4

^c^ = at V4 the OFC consist of one feeding of the cumulative dose only

Generic and disease-specific quality of life questionnaires (PedsQL, EQ-5D, FAQLQ, and FAIM according to age) will be conducted before and 2 weeks after V1, anytime between PC3 and V4, as well as 4 weeks after V4 (remainder at PC4). Eating habits will be assessed by questionnaire at screening and anytime between PC3 and V4. Burden of dietary behavior will be assessed using a visual analog scale at two time points during the intervention (V2 and between PC3 and V4). To assess possible GI complaints at screening, PC2, anytime between PC3 and V4, as well as in case of reported recurrent GI symptoms, the PEESS questionnaire will be filled out.

### Data collection and management

REDCap (Research Electronic Data Capture) will be used as electronic case report form (eCRF) to collect and manage the study data. REDCap is hosted at the Charité – Universitätsmedizin Berlin and provides an intuitive interface for data entry for clinicians. In addition, it provides a data integration platform for the data from the mechanistic subprojects. Audit-trails will be integrated for tracking data entries, corrections, and import/export procedures. A unique participant number will be assigned to every screened patient consisting with a prefix and a consecutive numbering. This unique code will identify all patient-specific data, e.g., clinical study data as well as biosample results. SAEs will be documented in the REDCap eCRF and on paper documents. Data access and storage will follow the data security concept of the Charité – Universitätsmedizin Berlin including password-protected access to all computers and folders, which contain sensitive data. Pseudonymized data will be made available to all participating partners of the CRU. Study data will be retained up to 15 years after study completion and publication of results.

### Sample size calculation

#### Randomized controlled trial

The sample size calculation is based on the difference in the primary endpoint (clinical tolerance to peanut or tree nuts after 1 year) between the two treatment groups (liberated diet versus complete allergen avoidance). Analyzing 48 patients per group (96 patients in total) would result in over 90% power to detect a difference in tolerance development of 30% (liberated diet group) vs. 5% (complete allergen avoidance group) after 12 months, based on a two-sided chi-squared test with significance level 5%. These estimates are based on data on natural clinical tolerance development with about 20% of peanut-allergic patients and about 10% of tree nut-allergic patients developing oral tolerance later in life [6, 7, 44], and after 1 year of strict avoidance diet about 5% of peanut-allergic patients show natural tolerance development [18]. To compensate for a potential dropout rate of at most 20%, 60 patients will be randomized into each group (120 in total).

#### Observational cohort

The cohort study is considered exploratory. No formal sample size calculation has been performed. A number of 120 subjects to be included were considered realistic.

### Planned analysis

#### Randomized controlled trial

The primary endpoint is the clinical tolerance to peanut or tree nuts after 1 year assessed by OFC (up to the repetitive cumulative dose). The primary analysis of the primary endpoint will be performed by logistic regression with (fixed) factor treatment group and the stratification variables age (1–5 years, 6–17 years, 18–67 years), allergen (peanut, tree nuts), and threshold level (5th–6th dose, 7th–repetitive cumulative dose) as fixed factors. From this model, an adjusted odds ratio will be calculated with 95% confidence interval and a *p* value for the treatment group comparison. The analysis will be performed on the full analysis set (FAS) of patients analyzed according to their randomization group without imputation of missing values. The significance level will be set to 0.05 (two-sided). All other analyses will be considered explorative.

Several explorative sensitivity analyses will be performed for the primary endpoint:
A re-run of the primary analysis model with the per-protocol (PP) population (instead of the FAS) will be performed.In case of relevant differences between the treatment groups with respect to baseline variables, the primary analysis will be repeated with further adjustment variables.Subgroup analyses will be performed regarding the following subgroups:

• Age (1–5 years, 6–17 years, 18–67 years)

• Allergen (peanut, tree nuts)

• Threshold level (5th–6th dose, 7th–cumulative dose)

• Severity grade of allergic reaction at initial OFC

• Peanut or tree nut sIgE at screening

The explorative analysis of secondary endpoints will follow the same principle as the primary analysis of the primary endpoint, i.e., models with (fixed) factor treatment group and the stratification variables age (1–5 years, 6–17 years, 18–67 years), allergen (peanut, tree nuts), and threshold level (5th–6th dose, 7th–repetitive cumulative dose) factors. Continuous outcomes will be analyzed by analysis of covariance (ANCOVA) with the respective baseline value as additional covariate. Secondary endpoints will generally be analyzed with the FAS; selected secondary endpoints will also be analyzed with the PP population.

Concerning safety endpoints, the nature, frequency, and severity of adverse events and safety variables, including serious adverse events, will be summarized descriptively by dietary intervention group.

As a general analysis strategy, missing data will not be imputed. No interim analyses for efficacy are planned. Further details will be described in the Statistical Analysis Plan (SAP), which will be finalized prior to data analysis.

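### The single confirmatory analysis, a logistic regression with about 2.4 expected control-arm events, can return an infinite odds ratio, and the power figure of over 90% belongs to a different test

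*Protocol article*

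**What the plan says.** Under Sample size calculation (Randomized controlled trial), the article states: "Analyzing 48 patients per group (96 patients in total) would result in over 90% power". The assumed effect is a "difference in tolerance development of 30% (liberated diet group) vs. 5% (complete allergen avoidance group) after 12 months", and the figure is "based on a two-sided chi-squared test with significance level 5" per cent. The randomised number then allows for dropout: "To compensate for a potential dropout rate of at most 20%, 60 patients will be randomized into each group (120 in total".

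Under Planned analysis (Randomized controlled trial), the method is different: "The primary analysis of the primary endpoint will be performed by logistic regression with (fixed) factor treatment group". The three stratification variables enter as further fixed factors: age in three classes, allergen in two and threshold level in two. The model is to yield an adjusted odds ratio with 95% confidence interval and a p value, tested two-sided at 0.05. Everything else is explorative, and missing values are not imputed.

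The article names neither the test behind the p value (Wald, likelihood ratio or score) nor a penalised or exact method. It leaves further details to a SAP that is not shown.

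**The concern.** Sizing a trial on a chi-squared test and analysing it by adjusted logistic regression is common and usually harmless. It is less harmless here because the avoidance arm is expected to produce only two or three tolerant patients. If that arm has no event, the treatment coefficient in a maximum-likelihood fit diverges. The odds ratio has no finite estimate, and its Wald interval and p value carry no information. This is the kind of result in which the liberated diet looks most effective.

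The unnamed test also matters. With so few control events, the usual candidates differ materially in both power and type I error, and the wording allows any of them. A method settled only once sparse data had been seen would be open to the charge that it was chosen for its result.

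**Working it through.** **Inputs.** From the article: 48 analysed per arm, 30% versus 5%, two-sided 0.05, 1:1 allocation, 60 randomised per arm. Assumption: logistic regression is fitted by ordinary maximum likelihood, since no other method is named.

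**1. The stated power reproduces.** The mean rate is (0.30 + 0.05)/2 = 0.175.
- Standard error under the null: √(2 × 0.175 × 0.825/48) = 0.0776.
- Standard error under the alternative: √((0.30 × 0.70 + 0.05 × 0.95)/48) = 0.0732.
- z = (0.25 − 1.96 × 0.0776)/0.0732 = 1.34, giving power of 91.0%.
- Enumerating all 2×2 tables gives 93.9% for the uncorrected Pearson test.
- 48/0.8 = 60 per arm, as stated.

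**2. Events available.** Control arm: 48 × 0.05 = 2.4. Liberated diet arm: 48 × 0.30 = 14.4. The model has five non-intercept coefficients: treatment, two for age, one for allergen and one for threshold.

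**3. Chance of no control-arm event.** 0.95^48 = 8.5%; with no dropout, 0.95^60 = 4.6%. The maximum-likelihood odds ratio for treatment is then infinite. Adding covariates cannot remove this, and choosing another test does not change the estimate.

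**4. Power by test at 30% versus 5%** (unadjusted model, exact enumeration):

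| Test | 48 per arm | 60 per arm |
|---|---|---|
| Pearson chi-squared | 93.9% | 97.1% |
| Logistic, Wald | 83.8% | 92.2% |
| Logistic, likelihood ratio | 94.0% | 97.7% |
| Firth, penalised likelihood ratio | 92.9% | 97.0% |

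The Wald test first reaches 90% at 57 analysed per arm (90.5%). At 48 per arm, chi-squared is significant and Wald is not in 10.1% of trials; 8.5 of those 10.1 points are trials with no control-arm event.

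**5. Type I error at 48 per arm** (unadjusted, exact):

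| Common rate | Chi-squared | Wald | Likelihood ratio | Firth |
|---|---|---|---|---|
| 5% | 5.2% | 0.1% | 8.9% | 4.3% |
| 10% | 5.9% | 2.2% | 6.1% | 4.8% |
| 17.5% | 5.4% | 4.5% | 5.6% | 4.7% |

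**6. The full planned model.** This was simulated with 4,000 trials per scenario at 48 per arm. The stratum shares are assumptions, as the article gives none: age 25/25/50%, allergen 50/50, threshold 50/50, with covariate effects set to none, moderate or strong. Trials with no control-arm event counted as not significant under Wald.
- Wald: 84.3%, 86.0% and 86.1%.
- Likelihood ratio: 93.9% to 96.6%.
- Score: 93.5% to 96.3%.

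A separate simulation with age shares of 25/30/45% gave 92.5% to 93.3% for Firth with a penalised profile likelihood, with type I error of 3–4% when both rates were 5–10%.

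**7. An example.** With 14/48 versus 0/48, Pearson chi-squared is 16.4 (p ≈ 0.00005). The maximum-likelihood odds ratio is infinite and a Wald test cannot reject. In the unadjusted case Firth's method adds one half to each cell, so the odds ratio is (14.5 × 48.5)/(34.5 × 0.5) = 40.8, which is finite.

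**The case against.** The sample size statement is accurate as written and names its test openly. The 84% belongs to a Wald test that the article never mentions; with a likelihood-ratio or score test the planned model exceeds 90%. Test statistic, interval method and sparse-data fallback are ordinary SAP content, and this is an abridged protocol. Also, 84% applies only if dropout reaches its stated maximum of 20%.

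Most of this stands and limits the point. A reader might infer any of three stronger claims, and the article supports none of them:

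- *That the power figure is wrong or the trial underpowered.* The figure is right for chi-squared. The shortfall depends on Wald being used and on about 48 per arm being analysed.
- *That too many covariates cause the loss.* Wald without covariates has 83.8% power, against 84.3% to 86.1% with them. Sparse control-arm events are the cause.
- *That a rescue method will be chosen after seeing the data.* The SAP is to be final before analysis and may already name one; this cannot be checked.

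The part that the objection does not answer is the estimator. The article itself fixes the model and the odds ratio as the confirmatory result, and under its own planning rates an ordinary fit has no finite estimate in about one trial in twelve. A likelihood-ratio test would rescue the p value but not the odds ratio, and it is anti-conservative at low rates.

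**Conclusion.** The point holds in limited form. Two sections that should describe the same test do not, and the analysis as fixed is fragile at the article's own rates. There is an 8.5% chance of an infinite odds ratio at 48 per arm (4.6% at 60), whichever test is used. Depending on a test that is not named, power at 48 per arm is about 84% (Wald) or about 94% (likelihood ratio), and type I error when both rates are 5% is 0.1% or 8.9%.

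These results assume ordinary maximum likelihood and the planning rates; a control rate above 5% would ease the problem. The event counts and unadjusted figures need no further assumption. The adjusted figures rest on assumed stratum shares but agree closely. Since this is the trial's only confirmatory test and the remedy costs little, the method should be settled before analysis.

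**What to change.** Keep the treatment factor and the three stratification factors. In Planned analysis, state that the primary model is fitted by Firth-penalised logistic regression, with the p value and 95% confidence interval from the penalised profile likelihood. In Sample size calculation, tie the power statement to that test: about 93% at 48 analysed per arm, with type I error of 4–5% at common rates of 5% to 17.5% (unadjusted, exact). If a Wald test is kept instead, name it and restate the power as about 84% at 48 per arm. If the SAP already specifies a penalised or exact method, only the power statement needs aligning.

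The cost is one added sentence, a software option and a slightly less familiar estimator. No extra patients, visits or data are needed.
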